## Introduction

Motor neuron disease (MND) is an incurable disease, that causes progressive weakness of muscles involving the limbs, speech, and swallowing, leading to progressive disability and eventual respiratory failure. In the United Kingdom, there are approximately 5000 people with MND at any one time [1]. The average life expectancy following diagnosis is 2 to 3 years but the course of MND can vary from only a few months to over 10 years. The distress and burden of the disease affects people with MND, their family, and caregivers and the relenting progression of disability causes social, emotional, and financial strain [2,3].

In the United Kingdom, multidisciplinary teams (MDTs) deliver specialist MND care through MND Care Centers or care networks across the country. Expert health care professionals (HCPs) monitor symptoms and offer interventions such as Riluzole, which can improve survival by approximately 2 to 3 months [4], gastrostomy feeding to promote good nutrition [4], or treatment of respiratory failure with noninvasive ventilation, which improves both quality of life and life-expectancy [5]. Attendance at specialist MND clinics has been reported to improve survival independent of these other interventions [6,7]. Traditionally, clinics are held at regular fixed intervals, approximately 3 months apart.

Despite the potential benefits of MDT care, this model is not always sufficiently responsive to the needs of patients because these can change rapidly, and therefore, can require people with MND and their families to undertake progressively more difficult journeys to the clinic at a time predicted by the clinician at their last meeting. Given the burden associated with traveling to the clinic, it is important that visits occur when they are most needed. Conversely, some people with MND whose needs may not change considerably over time, may not benefit from a clinic appointment every 3 months.

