### Engagement

Manually and automatically collected data at every site will be analyzed in accordance with an adapted version of the taxonomy of adherence Vrijens et al [26]. This will provide information relating to the uptake, initiation and discontinuation, persistence, nonpersistence, and activity of the TiM-C service.

Local HCPs will keep a record of the number of people with MND who have been invited to TiM-C and the reasons for people not creating an account if these are offered at the time of face-to-face invitation. The TiM-C system automatically collects the number of people with MND who create an account. The TiM-C system also automatically collects the number of caregivers who are invited and the number who create an account. Combining this data will provide information on uptake (the proportion of people with MND and caregivers who create an account when invited) at each site, in addition to reasons for nonuptake that can be used to develop the invitation process.

If available at the MND center, demographics and routinely collected data will be analyzed to investigate whether there are any statistically significant differences between those who do and do not create TiM-C accounts. Relevant data may include, age, gender, partial postcode (to explore the effects of deprivation), and outcomes relevant to MND such as functional rating, date of onset, site of onset, and date of diagnosis. Statistical analyses will include *t* tests and chi-square tests for parametric and nonparametric data, respectively.

The TiM-C system automatically collects anonymized data relating to the date and time people with MND and caregivers complete a questionnaire. This data will be analyzed to calculate initiation and discontinuation (the date of first and last questionnaire completion, respectively), persistence (the time from first to last questionnaire completion), nonpersistence (the time following persistence during which no questionnaires are completed), and activity (the percentage of questionnaires completed during persistence). Similar to the above, if data is available, statistical analyses will be conducted to investigate whether any aspect of engagement can be predicted by individuals’ demographics or disease-relevant data.

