### TiM-C Economic Evaluation (WP4)

This WP includes a health economic analysis of the TiM-C system, as it is implemented in MND specialist centers and networks across the United Kingdom. A cost-consequence analysis [31] will form the primary economic evaluation because TiM-C is a complex digital intervention with multiple possible effects, including both health and nonhealth outcomes, which makes the creation of a single measure difficult. A budget impact analysis [32] will also be conducted, to help future health care commissioners understand how the implementation of TiM-C may affect expenditure under different circumstances.

The cost-consequence analysis will only focus on costs for intervention delivery, as TiM-C is not designed to replace any part of usual care (ie, TiM-C will incur costs in addition to usual care, rather than accrue cost-savings). Per patient and caregiver costs incurred from the need for a HCP to regularly review user scores, will be calculated by asking HCPs to estimate how long it takes to review the account of a single user. This will be combined with unit costs of health, accessed from the Personal Social Services Research Unit. These will be combined with the central cost of TiM-C per MND service, which is already known, in addition to HCP time to receive the necessary training. Outcomes will be taken from the process evaluation and presented alongside the per-user cost of TiM-C to aid comparison.

A budget impact analysis will be conducted using the costs calculated as part of the cost-consequence analysis described above. Engagement data from the process evaluation will then be used to describe the cost of TiM-C for the MND center (in terms of HCP time and system cost) under different review protocols. For example, TiM-C does not dictate how often HCPs should review the system. The more often TiM-C is reviewed and the higher the user engagement from people with MND and caregivers, the more HCP time will be needed and the higher the associated costs. This analysis will display these different circumstances to aid health care commissioners in understanding the affordability of the TiM-C service.

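### Discontinuation and persistence, as defined, cannot separate users who stopped from users still active at the data cut or users who died

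*Protocol article*

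**What the plan says.** The Engagement section of the process evaluation (WP3) derives its measures from the automatically recorded times of questionnaire completion. It defines "initiation and discontinuation (the date of first and last questionnaire completion, respectively", then "persistence (the time from first to last questionnaire completion), nonpersistence (the time following persistence during which no questionnaires are completed", and finally "activity (the percentage of questionnaires completed during persistence". Where data are available, it plans analyses of "whether any aspect of engagement can be predicted by" demographics or disease-relevant data. Its examples of such data include functional rating and the dates of onset and diagnosis.

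The section gives no gap rule to tell a current user from one who has stopped, no censoring, and no end point for nonpersistence. It does not mention death here.

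Two other places bear on the point. The Introduction states: "The average life expectancy following diagnosis is 2 to 3 years". The Results part of the Abstract has 13 further centers starting from July 2024 and the study ending in November 2026.

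**The concern.** A last-completion date exists for every user with at least one completion, whatever ended the series. The label discontinuation therefore covers three different events: the user stopped, the user died, or the data were cut while the user was still active. Persistence inherits the same mixture. Nonpersistence, with no stated end, can run on after death.

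As a description of observed use this does no harm. It matters once the measures are put into a predictor analysis. Functional rating and the timing of onset and diagnosis plausibly track survival, and date of account creation fixes the follow-up available. Without censoring, a user with faster disease or a later start has shorter persistence even if neither ever disengages. The study could then report that sicker people disengage from telehealth when the data show only that they died sooner.

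Activity raises a lesser, related point. It is computed inside the persistence window only, so it leaves out everything missed after quitting.

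**Working it through.** The article states no expected engagement figure, so there is nothing to reproduce. The check applies the printed definitions to assumed cohorts.

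**Inputs from the article.** Average life expectancy 24 to 36 months after diagnosis (Introduction). July 2024 to November 2026 = 28 months at the 13 further centers (Abstract).

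**Assumptions, none of them in the article.** Accounts created uniformly over the first 16 of the 28 months, so follow-up f runs from 12 to 28 months. Exponential survival from account creation with mean m = 24 or 36 months. Exponential time to quitting. Four questionnaires a month unless stated. A true completion rate p = 0.7 while using the system.

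**Step 1. Nobody ever quits.** The true number of discontinuations is zero, yet every user is given a discontinuation date. The share of those dates due to death is 1 − (m/16)(e^(−12/m) − e^(−28/m)):
- m = 24: 1 − 1.5 × (0.6065 − 0.3114) = 0.56
- m = 36: 1 − 2.25 × (0.7165 − 0.4594) = 0.42

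The remaining 44% and 58% are users still active at the cut. Simulation of 100,000 users per scenario agrees (0.559 and 0.423). Mean nonpersistence is 5.1–6.9 months if counted to the cut and 0.23 months if it ends at death.

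**Step 2. What a predictor analysis would see.** Still with nobody quitting, expected time under observation is m(1 − e^(−f/m)), which persistence follows closely:
- f = 28: 24 × 0.6886 = 16.5 months against 36 × 0.5406 = 19.5 months. The difference is survival alone.
- f = 12: 24 × 0.3935 = 9.4 months and 36 × 0.2835 = 10.2 months. The drop from the f = 28 figures is late entry alone.

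**Step 3. Some users quit.**
- Mean time to quitting 24 months: 39.8–44.2% of recorded discontinuations are real, so 56–60% are deaths or current users. Median recorded persistence is 8.0–9.8 months, against a median time to quitting of 24 × ln 2 = 16.6 months in the absence of death and the cut.
- Mean time to quitting 60 months: 11.5–13.2 months against 41.6 months.

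**Step 4. Activity.** The first and last questionnaires in the window are completed by definition. With n scheduled, expected activity is (2 + (n − 2)p)/n for n ≥ 2, and 100% for n = 1. At p = 0.7:
- n = 2: 100%
- n = 4: (2 + 1.4)/4 = 85%
- n = 8: (2 + 4.2)/8 = 77.5%
- n = 26: (2 + 16.8)/26 = 72.3%
- n = 52: (2 + 35)/52 = 71.2%

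The excess over p is 2(1 − p)/n. At n = 26 that is 2.3 points for p = 0.7 and 5.4 points for p = 0.3, so it is large only in short windows. The omission of later missed questionnaires is larger: with a mean time to quitting of 24 months, activity is 0.74–0.75 as defined and 0.54–0.56 over all questionnaires due while alive and under observation.

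**The case against.** The strongest reply is that this is analysis-plan detail. The article condenses a fuller document, names no method for the predictor analyses of persistence, and makes them conditional on data being available. First date, last date and cut date are also the raw inputs that a censored analysis needs. This stands in part: a fuller plan may already handle censoring, so the results cannot be called wrong in advance. It does not remove the point, because the article does not leave the definitions open. It prints them, and followed as printed they label current users and people who have died as having discontinued.

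A reader might infer more than the article supports:
- *That the study deliberately counts death or the data cut as disengagement.* It never says so. This is a consequence of applying the definitions literally, and nonpersistence simply has no stated end.
- *That activity is invalid, or rises whenever people quit.* It is explicitly conditional on persistence and reported beside it, which is legitimate. At a constant completion rate it is inflated materially only in very short windows.
- *That site comparisons will be distorted.* Prediction is planned from individual characteristics. Only uptake is specified by site.
- *That the budget impact analysis is wrong.* The economic section (WP4) says "Engagement data from the process evaluation will then be used to describe the cost of TiM-C for the MND center", but does not name persistence or activity as the input. Health care professional log-ins are engagement data too, and review workload follows actual use whatever ends it.

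**Conclusion.** The point holds for discontinuation, persistence and nonpersistence, and for activity when it is read alone. As defined, the first three do not separate stopping from death or from continuing use at the cut, and the planned predictor analysis would confuse prognosis and follow-up time with disengagement. Given the stated life expectancy and a window of about 28 months, both kinds of misclassification will be common.

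The direction follows from the definitions. The sizes do not: 56–60% misclassified, or 8.0–9.8 against 16.6 months, rest on the assumed quit rate, entry pattern, survival shape, questionnaire interval and completion rate. The stated life expectancy runs from diagnosis, whereas users join at varying times after it. The one center already recruiting may also have longer follow-up than 28 months.

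Uptake and initiation are unaffected. Engagement is one of five components of the process evaluation. The wording should be settled before the engagement data are analyzed.

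**What to change.** - Define discontinuation as a prespecified gap without a completed questionnaire, scaled to the questionnaire schedule. A user whose last completion lies within that gap of the data cut is censored, not discontinued.
- Analyze time from first questionnaire to discontinuation with censoring at the data cut and death as a competing event. For caregivers, treat the death of the person they care for in the same way.
- Report cumulative incidence of discontinuation, and use cause-specific hazard models for the predictors.
- End nonpersistence at the earliest of death, account closure or the data cut.
- Keep activity during persistence, and add completed over sent for the whole period under observation.

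**Cost.** No new participants or visits, but more than wording. Date of death is not among the article's examples of routine data, and the completion times are described as anonymized. Death dates must therefore be obtained and linked where a center can supply them. The planned predictor analysis already needs person-level linkage of the same kind. Where a center cannot supply them, censor at last known contact from a source other than the questionnaires, and state the limitation. The engagement results will be less simple to present.

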### People With MND, Their Caregivers, and HCP (User) Experiences

All TiM-C users will be invited to complete a short questionnaire to assess the acceptability and feasibility of the system, 1 month and 12 months after they create their TiM-C accounts. Questions will be based on the Theoretical Framework of Acceptability [27].

Additionally, 10 semistructured interviews will be conducted with people with MND, their caregivers, and HCPs at 2 time points (60 in total) from up to 5 centers, to facilitate understanding of the experiences, perceived impacts on knowledge, and access to care, and potential unintended consequences of the TiM-C system. Interviews will be conducted after users have had their TiM-C accounts for 3 months and 12 months.

Interviews will use videoconferencing software (in line with participant preferences and permissions) or telephone. All interviews will begin with general, open-ended questions relating to the participant’s understanding of MND and their perception of the care they receive, or the participant’s role and experience with MND care. For people with MND and their caregivers, specific questions will then relate to their experiences of the TiM-C service and how this has affected their care. For HCPs, specific questions will relate to their understanding of MND in general and of the people with MND and caregivers using TiM-C. Further questions will be asked about how HCP’s use the TiM-C system and their perception of how it affects the care that they deliver.

The interviews will last approximately 30-60 minutes in duration and be conducted by members of the research team. Interviews will be audio-recorded and transcribed verbatim for analysis. All identifiable information will be removed during transcription with a pseudonym replacing the participant’s name. Participants will have the option to choose their own pseudonyms. An inductive reflexive thematic analysis [28] will be conducted by the research team using NVivo. The analysis will focus on semantic (as opposed to latent) meanings within the transcripts.

### Service Impact of TiM-C Upon MDT Care and the MND Service

To explore how TiM-C has affected the structure of each organization’s MDT care, the same survey completed to describe the service and local context (see “TiM-C process evaluation” section above) will be completed yearly after the first. Additionally, any audit on the MND MDT services conducted within the duration of this study will also be collected.

Semistructured interviews will be conducted with HCPs using the TiM-C system to explore their beliefs about their connectedness with users, timeliness of care, and the quality of care that they deliver. These questions will be asked at the same time as those described in 4.3.3 above, to reduce the burden the research has on participants.

To explore whether the TiM-C system has improved the experience of MND care for people with MND and their caregivers, participants will complete a patient-reported experience measure (PREM) 1 month and 12 months after they have been invited to create TiM-C accounts. Participants who have created an account will be allocated to the “user” group and those who do not create accounts will be allocated to the “non-user” group. The PREMs will be compared between these 2 groups across both data collection points. The PREM is adapted from the Client Satisfaction Scale [29].

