**Methods:**

WP1 will use semistructured interviews with 10-15 people involved in the approval of TiM-C to understand the barriers and facilitators to governance processes. WP2 will use individual and group interviews with 25-35 users (people with motor neuron disease, caregivers, HCPs, MND researchers, and industry) of TiM-C and TiM-R to understand the current unmet needs of these user groups and how TiM services can be developed to meet these needs. WP3 will use a process evaluation involving 5 elements; local context, engagement, user experiences, service impact, and mechanisms of action. A range of methods, including audits, analysis of routine data, questionnaires, interviews, and observations will be used with people with motor neuron disease, caregivers, and HCPs, both those using the system and those who declined the service when invited. WP4 will use data collected through the process evaluation and known costs to conduct a cost-consequence and budget impact analysis to explore the cost-benefit of the TiM-C service. Most data collected will be qualitative, with thematic and framework analysis used to develop themes from transcripts and observations. Descriptive statistics or *t* tests and chi-square tests will be used to describe and analyze quantitative data.

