From the perspective of individuals involved in the approval of National Health Service (NHS) services, what are the barriers and facilitators of approving TiM-C at scale?What are the unmet needs of people with MND, their caregivers, HCPs, MND researchers, and industry?How can TiM-C and TiM-R be developed to support end user needs?Does the use of the TiM-C service result in better MDT care for people with MND and their caregivers?What are the costs associated with the TiM-C service and how do they affect health care expenditure?

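### The user versus non-user PREM comparison has self-selected groups, no pre-exposure score and only unadjusted tests named, so it can show an association but not that TiM-C improved care

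*Protocol article*

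**What the plan says.** Research question 4 (Introduction) is worded causally: "Does the use of the TiM-C service result in better MDT care for people with MND and their caregivers". Within WP3, the section on service impact gives the PREM the same purpose: "To explore whether the TiM-C system has improved the experience of MND care for people with MND and their caregivers".

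The PREM is completed "1 month and 12 months after they have been invited to create TiM-C accounts". Invitees who open an account form the user group, and "those who do not create accounts will be allocated to the" non-user group. The Abstract (Methods) describes the WP3 participants as "both those using the system and those who declined the service when invited". The analysis is given in one sentence: "The PREMs will be compared between these 2 groups across both data collection points". That section names no test. The Abstract says that descriptive statistics or t "tests and chi-square tests will be used to describe and analyze quantitative data".

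Four other places bear on this:
- **Participants, Textbox 1:** patients and caregivers become eligible only once a month or more has passed since their invitation.
- **Engagement:** where a center holds the data, the study will examine "whether there are any statistically significant differences between those who do and do not create TiM-C accounts". The characteristics listed include age, gender, deprivation (through partial postcode), functional rating and date of diagnosis.
- **Nonexplicit Consent:** these routinely collected data are to be used for the engagement question and nothing else.
- **Limitations:** the absence of a randomized design is acknowledged. The self-selection of PREM users and non-users is not mentioned.

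**The concern.** Opening an account is the invitee's own decision. People who are less disabled, more at ease with technology or already content with their clinic may be more likely to sign up, and may also score their care differently whether or not they use TiM-C. A user versus non-user difference then mixes any effect of TiM-C with the reasons for signing up, and it can err in either direction: selection can pass for benefit or hide harm.

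The usual partial protections are a score taken before exposure and adjustment for characteristics that differ between the groups. The timing and eligibility rules exclude the first. The data-use restriction prevents the second from drawing on the routine data. At stake is whether centers deciding to keep TiM-C are told that it improved care when the evidence supports only an association.

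**Working it through.** **1. Purpose against design.**

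| Element | What the article fixes | Consequence |
|---|---|---|
| Purpose | Whether TiM-C improved experience (Service Impact; research question 4) | A causal contrast is needed |
| Groups | Account opened or not (Service Impact) | Self-selected |
| First score | 1 month after invitation (Service Impact); eligibility starts no earlier (Textbox 1) | No PREM before possible exposure |
| Tests named | t and chi-square (Abstract; Engagement) | Both unadjusted |
| Routine covariates | Engagement analysis only (Nonexplicit Consent) | As written, not usable to adjust the PREM |
| Limitations | No randomized design | Self-selection not named |

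A later analysis plan can add a regression model. It cannot supply a score that was never collected, nor use routine data that this document reserves for another purpose.

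**2. The plan's own figure.** There is none to reproduce. The article gives no sample size, SD, effect size or power for the PREM; everyone eligible is approached.

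**3. Illustration on assumed inputs.** None of these inputs comes from the article. Let SMD be the standardized user versus non-user difference in one characteristic, and r its within-group correlation with the PREM. With no true TiM-C effect, the spurious difference in SD units is d = SMD × r:
- 0.3 × 0.2 = 0.06
- 0.3 × 0.4 = 0.12
- 0.5 × 0.4 = 0.20

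With n1 users and n2 non-users, SE = √(1/n1 + 1/n2). The chance of p < 0.05 is Φ(d/SE − 1.96) + Φ(−d/SE − 1.96).

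Example with 500 respondents and 70% uptake: n1 = 350, n2 = 150, SE = √(1/350 + 1/150) = 0.0976. For d = 0.12, d/SE = 1.23 and the chance is 23.3%. For d = 0.20, d/SE = 2.05 and the chance is 53.6%.

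| Respondents | Uptake | d = 0.06 | d = 0.12 | d = 0.20 |
|---|---|---|---|---|
| 200 | 50% | 7.1% | 13.6% | 29.3% |
| 200 | 70% | 6.7% | 12.2% | 25.4% |
| 500 | 50% | 10.3% | 26.9% | 60.9% |
| 500 | 70% | 9.4% | 23.3% | 53.6% |
| 1000 | 50% | 15.8% | 47.5% | 88.5% |
| 1000 | 70% | 14.0% | 41.3% | 82.6% |

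The nominal rate is 5%. More respondents make a false signal more likely, because the bias stays fixed while the standard error shrinks.

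**4. What adjustment does.** In simulation (4000 replicates, 500 respondents, 70% uptake, no true effect), the unadjusted t test rejected in 24.0% (d = 0.12) and 52.3% (d = 0.20). A regression including the confounder rejected in 4.9% and 5.0%. This is the best case, with a single confounder that is fully measured.

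**5. Loss by 12 months.** The Introduction gives an average life expectancy of 2 to 3 years from diagnosis. Assuming exponential survival, 12-month mortality is:
- read as a median: 1 − 2^(−1/3) = 21% to 1 − 2^(−1/2) = 29%
- read as a mean: 1 − e^(−1/3) = 28% to 1 − e^(−1/2) = 39%

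The 12-month patient comparison is therefore among a selected remainder. Nothing in the article shows whether deaths would differ between the groups.

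**The case against.** The strongest reply is that this is an exploratory part of an openly non-randomized process evaluation. The PREM purpose is only to explore. The Limitations section concedes the lack of a randomized trial, gives reasons, and leaves the best evidence on effectiveness to a later study. That stands, and it lowers the severity. It does not remove the mismatch between causal wording and a self-selected contrast.

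Several stronger readings that a reader might draw are not supported:
- **That the PREM is the only comparative evidence for research question 4.** WP3 as a whole answers that question. It includes yearly site surveys, audits before and during the study, and interviews, and the components are triangulated. The PREM is the only user versus non-user outcome at participant level.
- **That the plan rules out adjustment.** The PREM section names no test, the Abstract is a summary, and a fuller plan may specify a model. Silence on covariates in an article is not itself a fault. The finding rests on what the article does fix: grouping, timing, wording and the restriction on routine data.
- **That the plan predicts the groups will differ.** It says it will investigate whether they do.
- **That change cannot be examined at all.** A comparison of change from 1 to 12 months is possible. Clinics are about 3 months apart, so the 1-month score may be an early reference for some users, but an imperfect one because exposure may have begun.
- **That the PREM is known to enter the cost-consequence analysis.** The economic section takes outcomes from the process evaluation without naming it.

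**Conclusion.** The concern holds in limited form. A PREM difference between users and non-users, collected and compared as the article describes, cannot show that TiM-C improved the experience of care; it can show an association. This follows from the design as written and needs no numerical assumption.

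The size of the bias is unknown. The 7% to 89% range depends wholly on assumed imbalance, correlation, uptake and respondent numbers; it shows what is possible, not what is likely. The mortality range depends on an exponential assumption and on life expectancy counted from diagnosis.

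This should be fixed, but it does not undermine the whole evaluation: the component is exploratory, the lack of randomization is disclosed, and other WP3 evidence bears on the same question.

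**What to change.** 1. Collect age, gender, deprivation, functional rating and time since diagnosis on the PREM form, under PREM consent. Make the main PREM analysis a regression adjusted for these and for site, in place of t or chi-square tests. This avoids relying on routine data restricted to the engagement question.
2. Report the number of deaths and of non-responders at 12 months, by user and non-user group.
3. Report the result as an association. Reword the statement that TiM-C improved experience, and the answer to research question 4, to match. Name self-selection in the Limitations section.

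**Optional, at sites not yet open:** a PREM at invitation, used as a baseline covariate, with the eligibility line changed. The Abstract reports recruitment at 1 site, with 13 more from July 2024, so this could have covered most centers. It is not a requirement, because it places research consent ahead of an invitation to a clinical service and could affect uptake.

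**Cost:** a few extra form items for participants, the matching changes to study documents, and analyst time. Adjustment deals only with measured characteristics; unmeasured confounding remains, so item 3 is needed whatever model is used.
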